#### Accident-Related Measures

Regarding the accident, we ask for a short description of the event, the time that has passed since, and its subjectively perceived severity.

Pain due to the accident is assessed by the Brief Pain Inventory [37], which consists of 15 items. After the question of whether there is any pain that exceeds the normal levels expected in everyday life, participants have to indicate where the pain is located and how severe the limitations in various areas of life are due to the pain. We also assess the participants’ own perception of their physical attractiveness. Physical attractiveness is a very influential informational cue that is used frequently and consistently [38,39]. It has been shown to play an important role in how a person is perceived and responded to in many areas of life [38]. This includes health and psychological well-being. Bordieri et al [40] found that physical attractiveness influenced how others make attributions concerning the cause and prognosis of someone’s disability. Physical attractiveness was also linked to self-esteem [40]. Among the possible consequences of an accident is skin scarring. In most cases, this is perceived as unattractive [41]. Brown et al [41] found that skin scars impact a person’s acceptability to others as well as themselves and also have an effect on social functioning and emotional well-being. Thus, participants in this study are asked to rate their own physical attractiveness compared to that of other people their age. They also have to indicate how often they think about being rated by others in terms of physical attractiveness. Furthermore, the participants assess if and how much their own perception of their physical attractiveness has changed since the accident.

#### Cost-effectiveness Measures

Two questionnaires, each with a different emphasis, are used to assess the cost-effectiveness of the SelFIT program. The costs of health care consumption and productivity loss are assessed using the Treatment Inventory of Costs in Psychiatric Patients [42], a self-report questionnaire with 23 items of varying answer formats. Work-related factors with regard to the consequences of the accident are assessed by means of the Work and Health Questionnaire [43]. This questionnaire consists of 3 different parts with a total of 21 items with varying answer formats. The first part contains 5 items on current work activity, the second part contains 7 items on workload and cooperation, and the third part contains 9 items on health and well-being.

#### Embitterment and Optimism

We also assess embitterment and optimism. The Bern Embitterment Inventory [44], an 18-item questionnaire with answers ranging from 0=not at all true to 4=exactly true, is used to survey embitterment. Optimism is assessed as a predictor at the baseline measurement with the Life Orientation Test Revised [45], which consists of 10 items with answer categories ranging from 0=strongly disagree to 4=strongly agree.

General well-being and the ability to cope in everyday life are assessed by the Short Form 12 Health Survey [46]. The questionnaire consists of 12 items with different answer designs and options.

#### Self-esteem, Self-efficacy, and Emotion Regulation Skills

Furthermore, we assess self-esteem, self-efficacy and emotion regulation skills. Self-esteem is measured using the Rosenberg Self-esteem Scale [47]. This scale consists of 10 items with a 4-point scale from 0=strongly agree to 3=strongly disagree.

The General Self-Efficacy Scale [48] serves as a measure to assess perceived self-efficacy, aiming to predict coping with daily hassles and general adjustment after experiencing a stressful life event. The scale comprises 10 items on a scale from 1=not at all true to 4=exactly true. Emotion regulation skills are assessed via the Self-Report Measure for the Assessment of Emotion Regulation Skills [49], a 27-item questionnaire with answers ranging from 0=not at all to 3=(almost) always.

#### Program-Related Measures

The program-related factors we survey include user satisfaction and program usability. This is assessed using the Client Satisfaction Questionnaire [50,51], an 8-item scale with a 4-tiered answer format varying in its wording. The program’s usability is measured with the System Usability Scale [52], which consists of 10 items with answers ranging from 1=do not agree at all to 5=completely agree.

A further program-related factor is adherence, measured by the frequency and duration of use. Those parameters are gathered within the program by means of, for example, the number of log-ins or the percentage of pages and segments that have been accessed and browsed through at least once.

#### Demographic Variables

Demographic variables obtained from the first online questionnaire include gender, age, family status, and level of income and education. Additionally, participants are asked to indicate whether they have received or currently receive any treatment for mental health issues or physical rehabilitation.

### Data Collection and Management

All data is assessed online, either within the program platform or via online questionnaires programmed in Qualtrics [53]. Data integrity is enforced through different mechanisms including referential data rules, valid values, range checks, and consistency checks. The option to choose a value from a list of valid codes and a description of what each code means will be available where applicable. Checks are applied at the time of data entry into a specific field. All data is stored in anonymous form and can only be traced by a code that cannot be linked to the identity of the participant. Data gathered within the program as well as the program itself are stored on a firewall-encrypted backed-up server of the University of Bern. Only researchers directly involved in the study have access to the data, and they are subject to professional discretion.

### Power

In order to specify the sample size needed for the planned analyses, we conducted a power analysis based on a probability level of .05 and a power of 0.80 using G*Power (Heinrich-Heine-Universität Düsseldorf) [54]. To test the program’s efficacy compared to the control group, we expect small-to-moderate effect sizes between *d*=0.2 and *d*=0.35 as well as a correlation between the groups of *r*=0.4. Those estimates are based on the results of previous web-based interventions for adjustment problems [29].

The a priori power analyses yielded a necessary sample size of 80 (for *d*=0.35) to 238 (for *d*=0.2) participants in total for this analysis. Since the program does not include weekly guidance but rather guidance on demand, we expect slightly smaller effect sizes. Based on these calculations and assumptions we decided to target a sample size of N=240 participants.

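### The 80% power stated for d=0.2 to 0.35 against control does not follow: the totals 238 and 80 fit between-group differences twice that size

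*Protocol article*

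**What the plan says.** All of this stands in the Power section of the protocol article unless another section is named.

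- Error rates and software: "a power analysis based on a probability level of .05 and a power of 0.80 using G*Power". Sidedness is not stated.
- Effect: "To test the program’s efficacy compared to the control group, we expect small-to-moderate effect sizes between" d=0.2 and d=0.35. The d is therefore tied to the comparison of programme with control.
- Correlation: "as well as a correlation between the groups of" r=0.4.
- Result: "The a priori power analyses yielded a necessary sample size of 80" (for d=0.35) to 238 (for d=0.2) "participants in total for this analysis".
- Expectation and choice: because guidance is only on demand, "we expect slightly smaller effect sizes", and "we decided to target a sample size of N=240 participants". The target thus follows the d=0.2 end of the range.

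Elsewhere, the Randomization section describes two arms allocated 1:1. The Statistical Analysis section plans linear mixed models of change from baseline, compared between groups and over the measurement points. The Study Design section gives visits at baseline and weeks 4, 8, 12, 24 and 36, with control participants gaining access after 12 weeks.

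**The concern.** For two independent arms, 238 people in total is far too few to give 80% power for a standardised difference of 0.2, and 80 is far too few for 0.35. The description of r is a second sign of trouble. Separately randomised people have no correlation between groups, so 0.4 can only be a correlation between repeated scores of the same person. Both signs suggest that a between-group d was put into a formula for within-person or interaction effects without the right conversion.

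This calculation is the only stated basis for N=240. If it is wrong, the trial claims 80% power at the low end of its expected range when the true figure is well below that. A non-significant result could then be read as evidence against an effect of d=0.2 when the trial had a large chance of missing it.

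**Working it through.** **Inputs.** From the Power section: alpha 0.05 (two-sided taken), power 0.80, d=0.2 and 0.35, r=0.4, N=240. From the Randomization section: 1:1, so 120 per arm. Complete data are assumed throughout.

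**1. Reproduce 238 and 80.** For a repeated-measures within-between interaction with 2 groups and m=2 time points, the noncentrality is λ = f²·N·m/(1−r), with 1 and N−2 degrees of freedom. Enter f=d/2.

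- d=0.2, f=0.10: λ = 0.01×238×2/0.6 = 7.93, power 0.801. N=236 gives 0.798, so 238 is the smallest even total.
- d=0.35, f=0.175: λ = 0.030625×80×2/0.6 = 8.17, power 0.806. N=78 gives 0.796, so 80 is the smallest even total.

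Both printed totals match. With 3 to 6 time points the same routine gives 196/66, 166/56, 146/48 and 130/44, so only two time points fit. A two-sided paired t-test gives 238 and 79, a near miss.

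**2. What f=d/2 means here.** With arms equal at baseline and differing by d at follow-up, the interaction deviations in the four cells are ±d/4. Hence f=d/4, and the between-group difference in change is 4f. The values used give 4×0.10 = 0.40 SD and 4×0.175 = 0.70 SD, twice the stated 0.20 and 0.35.

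**3. Same routine with f=d/4.** For d=0.2 and N=240: λ = 0.05²×240×2/0.6 = 2.00, power 29%. The totals needed for 80% are 944 (d=0.2) and 310 (d=0.35).

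**4. Check by two-sample noncentral t, one post-baseline visit.** With n=120 per arm, the noncentrality is d·√(n/2)/√k. The variance factor k is 2(1−r)=1.2 for change, 1 for the follow-up score and 1−r²=0.84 for a baseline-adjusted score. For d=0.2 this is 1.41, 1.55 and 1.69.

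| | Change | Follow-up score | Baseline-adjusted |
|---|---|---|---|
| Power, N=240, d=0.2 | 29% | 34% | 39% |
| Power, N=240, d=0.35 | 69% | 77% | 84% |
| Power, N=80, d=0.35 | 29% | 34% | 39% |
| Total N for 80%, d=0.2 | 944 | 788 | 662 |
| Total N for 80%, d=0.35 | 310 | 260 | 218 |
| d with 80% power at N=240 | 0.40 | 0.36 | 0.33 |

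**5. Use of several visits.** Assume a constant effect averaged over weeks 4, 8 and 12, with all correlations 0.4. The mean of three scores has variance (1+2×0.4)/3 = 0.6. So k = 0.6+1−0.8 = 0.8 for change and 0.6−0.16 = 0.44 baseline-adjusted. At d=0.2 power is 41% and 64%; at d=0.35 it is 86% and 98%.

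**The case against.** **The analysis is not a single contrast.** The Statistical Analysis section plans mixed models over several visits, and three of these fall by week 12. This stands as a limit on scope. A reader might infer that power at d=0.2 is 29% to 39% in any case, or less than half of 80%. The documents do not support that, because those figures hold for one post-baseline visit only. Under the constant-effect assumption the range is 41% to 64%, which is still below 80%. Visits after week 12 are no longer a comparison with untreated controls.

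**Kinder assumptions come close to 80%.** One-sided testing of the baseline-adjusted three-visit mean gives 75% at r=0.4 and 81% at r=0.6. Two-sided with r=0.7 it gives 79%. A single baseline-adjusted visit would need r slightly above 0.83. The article states r=0.4 and no higher value, and at r=0.4 none of these readings reaches 80%.

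**The routine is inferred.** G*Power is named but no test family or conversion of d is given, so the totals are reproduced by the interaction test rather than shown to come from it. This stands. The shortfall in step 4 does not depend on which routine was used.

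**The wording about r may just be loose.** It may well be. It needs correcting but does not prove the error by itself.

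**An article condenses the protocol.** That would excuse an omission. Here the inputs, the result and the claim are all printed, and they do not fit together.

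**Conclusion.** The power statement is wrong as written. The printed totals correspond to between-group differences in change of 0.40 and 0.70 SD, twice the stated d. At N=240 and d=0.2, power at one visit is about 29% on the planned change from baseline, 34% on the follow-up score and 39% baseline-adjusted. It is about 41% to 64% if a constant effect is averaged over weeks 4, 8 and 12. These figures assume two-sided 0.05, r=0.4 and complete data.

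Two stronger conclusions do not follow. A reader might infer that the trial could not detect d=0.2, but low power is not inability to detect. A reader might also infer that 240 is too few across the whole stated range. At d=0.35 it gives 69%, 77% or 84% at a single visit, so the upper end is reasonably covered.

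**What to change.** Keep N=240 and rewrite the Power section:

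1. Delete the claim that 80 to 238 participants give 80% power.
2. Describe r=0.4 as the correlation between repeated scores within a person.
3. Restate power for the analysis actually planned. For a week-12 change from baseline with complete data, 240 participants give 80% power for d of about 0.40 and about 29% for d=0.2. Quote about 0.33 and 39% only if the model is specified as baseline-adjusted, because the Statistical Analysis section currently names change from baseline and no baseline covariate.
4. Add that dropout can lower these figures; the Introduction itself reports high dropout in two comparable programmes.
5. Add that a non-significant result does not exclude d=0.2.

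The cost is rewording one section and a less favourable stated power. No extra participants are needed.

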In recent years, various web-based treatment options for adjustment problems and disorders have been developed. One of them is Trastornos Adaptivos Online [23,24]. The guided program comprises psychoeducational elements, strategies from positive psychology, and techniques to manage negative emotions and improve problem solving. In addition to the program, participants receive short weekly therapist support via telephone. Trastornos Adaptivos Online was well received by both clinicians and patients in a pilot study [24]. The program is currently being tested for its effectiveness in an RCT [23].

A further web-based intervention for the treatment of adjustment disorders is the Brief Adjustment Disorder Intervention [25,26]. This program is unguided and consists of four modules, which the participants can process in a self-determined order. The program’s theoretical approach is mainly CBT-based but also contains elements of mindfulness as well as findings from research on stress and coping [27]. Preliminary results of an RCT indicate that participants who used the program at least once within a month showed a decrease in symptoms of adjustment disorders and an increase in psychological well-being. However, there was a very high dropout rate, which is mentioned as the study’s most prominent limitation [26]. The authors tested the effects of additional therapist support on the program’s effectiveness. The additional support did not contribute significantly to the study’s outcomes [26]. This supports previous findings by Maercker et al [28] that web-based self-help interventions may be a promising treatment option for adjustment problems and further indicates that such interventions do not necessarily need scheduled guidance from a specialist.

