Another unguided web-based program for adjustment problems is ZIEL (German acronym: Zurück Ins Eigene Leben; “back to your own life”) [29]. The ZIEL program comprises different evidence-based techniques from treatments for depression, anxiety disorders, and post-traumatic stress disorders. ZIEL consists of 5 sections which participants can work through freely and as needed over a course of 4 weeks. In an RCT, the participants of both the experimental and the control group showed an improvement in the severity of symptoms of adjustment problems. The intervention group, however, showed a significantly greater improvement in terms of depressive symptoms and quality of life. However, the authors of ZIEL also report challenges with a high dropout rate and suggest different measures to address this. One of these suggestions is to focus on certain subgroups of people with adjustment problems or on certain triggers of adjustment problems. This, in turn, would allow for a more tailored response to the needs of the users, thereby creating a better user-program fit and greater relevance for the users [29].

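### The target of 240 randomised is the no-dropout requirement for d=0.2 plus two people, so the stated 0.80 power at d=0.2 has no room for missing outcomes.

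*Protocol article*

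**What the plan says.** The Power section of the protocol article describes a calculation "based on a probability level of .05 and a power of 0.80". Its other inputs are the statements "we expect small-to-moderate effect sizes between *d*=0.2 and *d*=0.35" and "a correlation between the groups of *r*=0.4", both attributed to earlier work on web-based programmes for adjustment problems, with the ZIEL trial (reference 29) as the source. The calculation "yielded a necessary sample size of 80 (for *d*=0.35) to 238 (for *d*=0.2) participants in total". Because guidance is only on demand, the authors add that "we expect slightly smaller effect sizes", and the section closes: "Based on these calculations and assumptions we decided to target a sample size of N=240 participants". No attrition allowance is mentioned. The Methods part of the Abstract makes clear that the 240 are people to be randomised, not completers.

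The Introduction, under Web-based Psychological Interventions, discusses two comparable randomised trials with results. Of the Brief Adjustment Disorder Intervention trial it says "there was a very high dropout rate" and treats this as that study's main limitation. Of ZIEL it says that the authors "report challenges with a high dropout rate". Neither statement comes with a percentage.

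Two other sections bear on the point. Study Design says that participants who drop out are still asked to complete the remaining assessments. Statistical Analysis plans an intention-to-treat analysis with multiple imputation and linear mixed models over the measurement points.

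**The concern.** A required sample size from a power routine counts participants who contribute the outcome. A recruitment target counts people randomised. Here the two differ by 2 in 240, or 0.8%, in a field where the document itself describes dropout as a serious problem. The plan takes its effect sizes from the ZIEL trial but carries over nothing about that trial's attrition.

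If more than about 1% of participants lack the outcome, the stated 0.80 at d=0.2 is no longer what the plan's own calculation gives. A reader of a null result would then credit the trial with more ability to detect d=0.2 than it had.

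**Working it through.** **Inputs.** From Power: alpha 0.05, power 0.80, d=0.2 to 0.35, r=0.4, stated requirement 80 to 238, target 240. From Randomization: 1:1 allocation. Assumed: 10% to 40% of participants without the outcome, since the document gives no rate.

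**Reproducing the plan's figures.** The routine that returns both stated numbers is the repeated-measures within-between interaction with 2 groups and m=2 measurements, entering f = d/2 and taking r as the correlation between repeated measurements:

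λ = N × m × f² / (1 − r), with 1 and N − 2 degrees of freedom, noncentral F, N rounded up to an even number.

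- d=0.2 (f=0.10): N=236 gives λ = 236 × 2 × 0.01 / 0.6 = 7.87, power 79.8%. N=238 gives λ = 7.93, power 80.1%. Requirement: 238, as stated.
- d=0.35 (f=0.175): N=78 gives λ = 78 × 2 × 0.030625 / 0.6 = 7.96, power 79.6%. N=80 gives λ = 8.17, power 80.6%. Requirement: 80, as stated.

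The formula has no dropout term, so no allowance is hidden in 238. With 3, 4 or 6 measurements the requirement at d=0.2 would be 196, 166 or 130, so the plan's figures come from the two-measurement version.

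**Where 80% is lost.** At d=0.2, 240 complete gives λ = 8.00 and power 80.4%. With 237 (just over 1% missing) power is 79.9%.

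**Power from 240 randomised, same method.** The last column is the d at which the same formula gives 80% power for that number of completers.

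| Missing (assumed) | Completers | λ at d=0.2 | Power, d=0.2 | Power, d=0.25 | Power, d=0.35 | d detectable with 80% power |
|---|---|---|---|---|---|---|
| 0% | 240 | 8.0 | 80.4% | 94.1% | 99.9% | 0.20 |
| 10% | 216 | 7.2 | 76.2% | 91.6% | 99.7% | 0.21 |
| 20% | 192 | 6.4 | 71.1% | 88.2% | 99.3% | 0.22 |
| 30% | 168 | 5.6 | 65.3% | 83.7% | 98.5% | 0.24 |
| 40% | 144 | 4.8 | 58.6% | 77.6% | 96.8% | 0.26 |

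**What an allowance would have cost.** Keeping 238 completers means randomising 238 / (1 − missing rate): 265 at 10%, 298 at 20%, 340 at 30% and 397 at 40%.

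**The case against.** The strongest reply has four parts.

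1. **Nothing is miscalculated.** Both 80 and 238 reproduce, and the authors chose the most demanding end of their range. This stands: the fault is an omitted planning assumption, not an arithmetical slip. A reader might infer that the trial is underpowered across its whole expected range, and the table does not support that. With 30% missing, power is 65% at d=0.2 but 84% at d=0.25 and 98.5% at d=0.35. The low end still matters, because it sets the 240 and because the text says "we expect slightly smaller effect sizes".

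2. **The planned analysis is not a completers' pre-post test.** The mixed model uses all randomised participants and the week 4 and week 8 data, and missing values are imputed. In the same routine with four measurements, f=0.1 and r=0.4, power is 93% with 240, 86% with 192 and 81% with 168. Those figures hold f fixed across all measurements, so they are only indicative and do not establish power for a week-12 contrast. They do show that the table treats anyone missing week 12 as contributing nothing, which is pessimistic. What stands is that part of the loss may be recovered, by an amount the document does not allow one to quantify. Imputation does not bring back unobserved week-12 information, and Power does not offer any of this as a reason for omitting an allowance.

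3. **Reported dropout need not mean missing questionnaires.** The Introduction does not say whether the earlier trials lost people from the programme or from assessment. Study Design asks those who drop out to keep answering, reminder emails are optional, and the narrower target group follows a suggestion made to address dropout. Retention may therefore be better than in the earlier trials. Nothing in the document supports a loss below about 1%, which is what 240 implies. Equally, no particular missing rate can be read from it.

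4. **The full protocol may contain the allowance.** It cannot do so without contradicting the article: the article gives both the requirement and the final number randomised, and they differ by two.

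**Conclusion.** The point holds at d=0.2. The target of 240 randomised contains an allowance of two people, and the stated 0.80 falls away once more than about 1% lack the outcome. On the plan's own method the loss is modest at 10% missing (76%) and material at 30% (65%). Seen as detectable effect, it moves from 0.20 with everyone complete to about 0.24 with 30% missing.

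This rests on three assumptions: the missing rates are illustrative; the reconstructed two-measurement calculation is the one the authors ran, which the exact match at both ends supports; and participants without week-12 data add nothing, which overstates the loss to an unknown degree. The result does not depend on whether d=0.2 was translated correctly into the power routine, because the plan's conversion is taken as given.

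**What to change.** Keep 240 randomised. In Power, state the expected week-12 questionnaire completion rate and its basis, and replace the unqualified 0.80 with the power at d=0.2, or the smallest d detectable with 80% power, at that number of completers. Use the same method as the final sample size calculation, so that the new figure and the 238 are comparable. If 30% missing were expected, the sentence on the present method would report 168 completers, 65% power at d=0.2, and 80% power at about d=0.24. If the authors want credit for the week 4 and week 8 data, they should show power for the planned mixed model under stated assumptions.

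The cost is one sentence and a less favourable stated figure. No extra participants are needed, which matters given the slow recruitment described in Results.
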